**3.18 Ethical Consideration**

Ethical approval will be sought from the UPM Ethics Committee for Human Research before the study will be conducted. Ethical clearance will also be obtained from the Kintampo Health Research Centre Institutional Ethics Committee. Permissions will be sought from the Ministry of Education, headmasters/headmistresses, and Chairpersons of Parent Teacher Association (PTA) of selected schools. The study will be registered with the Pan African Clinical Trials Registry. A written and signed informed consent from all participating students and their parents or guardians will be obtained and forms will be kept under lock and key at the office. Students will be informed that they could withdraw from participating in the study at any time. To ensure confidentiality, a code number will be given to each student in both the intervention and control groups and they would be asked to use the codes on their completed questionnaires.

**APPENDICES**

**Appendix A**

**QUESTIONNAIRE**

**EFFECTIVENESS OF BEHAVIORAL MODIFICATION INTERVENTION TO REDUCE CARDIOVASCULAR DISEASE RISK FACTORS AMONG PUBLIC SECONDARY SCHOOL STUDENTS IN BRONG AHAFO, GHANA.**

**Instructions (To be read out to students)**

The purpose of this questionnaire is to evaluate the effectiveness of a behavioral

modification intervention module on reducing cardiovascular disease risk factors among secondary school students in Brong Ahafo Region. Truthful responses are required. Information is strictly for research purposes and confidentiality is assured.

**SECTION 1: BACKGROUND INFORMATION** School code: Student code: District:

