**3.11 Intervention**

At this stage permissions and consent would had been sought from the Ministry of Education, District Directors of Education, Chairmen of the Parent Teacher Associations, parents/guardians, and students to carry out the study. All materials for the study will be ready at this stage. The objectives of the study and the eligibility criteria to participate in this study will be explained to all the students’ involved. Students will go through medical check-up which will be carried out by the two clinicians in order to pass eligibility criteria to be enrolled into the study.

The self-administered questionnaire will be given to students to complete. Health staff will measure students anthropometric and blood pressure measurements. Confidentiality and anonymity will be assured at all stages of the study. The module will be implemented in the intervention schools for a period of six months but not in the control schools. Then at the end of six months the same questionnaire will be given to students in both the intervention and the control schools. Health staff who will not take part during the baseline data collection will take anthropometric and blood pressure measurements of students at post intervention study. A total of 848 students will participate in the study; intervention (424) and the control (424) schools. Contamination of the intervention will be prevented by having intervention and control schools with distances between them.

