**3.12.1 Study Instruments**

A self-administered questionnaire, which will be validated and pre-tested will be used to collect data. Weight and height scales will be used to collect data on body weight and height measurements of students respectively. Then a diastolic and systolic apparatus will be used to measure blood pressure of participants. Body weight, height, diastolic, and systolic blood pressure measurements will be taken by the health staff.

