Section five consists of physical activity questionnaire (PAQ-A) for secondary school students (Kowalski, Crocker, & Donen, 2004). This is a 7-day recall instrument which will be administered in a classroom setting to assess general levels of physical activity among secondary school children. Students will be informed before this section is administered that is not a test but a tool for assessing actual physical activity during the past seven (7) days. Each physical activity item will be scored on a five (5) point scale. The value from one (1) to five (5) for each of the items used in the physical activity composite score, then the mean of the items which resulted in the final PAQ-A activity summary score.

Section six will be the modified CVD knowledge assessment questionnaire which comprise of meaning of CVDs, risk factors and preventive strategies of CVDs to assess CVD knowledge score among respondents. The school-based instrument was developed by George et al. (2013) to assess CVD knowledge levels among students. The scoring of the instrument is in the form of true or false questions and unsure (don’t know) response for each question. Respondents are to choose either true, false or ‘’don’t know’’ by circling in the provided box. Each correct answer will be awarded one score. The maximum score is 26 and the minimum score is 0.

Section seven and eight are the Motivation and Behavior skills respectively, which are the modified versions of the LifeWindows Information-Motivation-Behavioral skills questionnaires (The LifeWindows Team, 2006) which constructs were originally developed by (Fisher, Fisher, Amico, & Herman, 2006). Motivation constructs assess questions on personal and social motivation relating to how motivated or encouraged participants are to perform a CVD risk factor reduction lifestyle. Scoring of responses are based on the likert scale from ‘I strongly disagree to I strongly agree’. Each of the items are scored based on the responses from 0 to 3;

with strongly disagree as 0 to strongly agree as 3. All reverse items will be scored asuch before the final scores are determined.

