**3.15.2 Dependent Variables**

The dependent variables of this study are sub divided into primary and secondary outcomes. There were;

i. The primary outcomes are CVD knowledge and its risk factors, motivation, behavioral skills, physical activity, smoking, alcohol consumption, and dietary intake.

ii. The secondary outcomes are body weight, BMI, diastolic and systolic blood pressures.

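### The questionnaire's title and read-out script announce the effectiveness hypothesis just before six self-reported primary outcomes are collected from students who know their arm

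*Protocol*

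**What the plan says.** The questionnaire in Protocol Appendix A is titled "EFFECTIVENESS OF BEHAVIORAL MODIFICATION INTERVENTION TO REDUCE CARDIOVASCULAR DISEASE RISK FACTORS AMONG PUBLIC SECONDARY SCHOOL STUDENTS". Under the heading for instructions to be read out to students, the script begins "The purpose of this questionnaire is to evaluate the effectiveness of a behavioral" and continues "modification intervention module on reducing cardiovascular disease risk factors among secondary school students in Brong Ahafo Region". It then adds: "Truthful responses are required. Information is strictly for research purposes and confidentiality is assured".

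Section 3.11 fixes the second use of the form: "Then at the end of six months the same questionnaire will be given to students in both the intervention and the control schools". Section 3.12.1 fixes the mode of collection: "A self-administered questionnaire, which will be validated and pre-tested will be used to collect data". Section 3.15.2 fixes what depends on it: "The primary outcomes are CVD knowledge and its risk factors, motivation, behavioral skills, physical activity, smoking, alcohol consumption, and dietary intake". Body weight, BMI and blood pressure are secondary outcomes.

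Section 3.8 calls the trial single-blind and names only the health staff who take anthropometry and blood pressure as blinded. Section 3.14 gives the intervention schools three visits a week for six months. Under Section 3.5.2, schools are allocated after baseline data collection.

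**The concern.** Students in the intervention schools cannot be unaware of the programme by six months. Immediately before they answer, the title and script tell them that the form judges that programme, and which direction counts as success. Students in the control schools hear the same words but have had no programme to vouch for. The cue can therefore act differently in the two arms.

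If it does, the difference appears only at follow-up, because allocation comes after baseline. Adjusting for baseline cannot remove it. A reporting shift on a self-reported outcome looks the same as a treatment effect, and the protocol describes no objective check of smoking, alcohol, activity or diet.

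**Working it through.** **1. Which primary outcomes are exposed.** Each outcome in Section 3.15.2 is set against its section of the form (Section 3.12.2 and Appendix A).

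| Primary outcome | Form section | How it is obtained | Neutral statement in that section |
|---|---|---|---|
| Diet | 2 | Seven-day recall of amount and frequency | None |
| Smoking | 3 | Self-reported use | Yes, shared with alcohol |
| Alcohol | 4 | Self-reported use | Yes, shared with smoking |
| Physical activity | 5 | Seven-day recall | Yes |
| Knowledge | 6 | True, false or don't know, scored 0 to 26 | Introduced as a test |
| Motivation | 7 | Four-point agreement scale | None |
| Behavioral skills | 8 | Four-point hard-to-easy scale | None |

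For knowledge, Section 3.12.2 says "Each correct answer will be awarded one score". A wish to please does not supply the correct answer. That leaves 7 − 1 = 6 outcomes that a student can shade. Three of the six (diet, motivation, behavioral skills) have no neutral statement of their own, so the opening script is their main framing.

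**2. Scale, continuous scores.** The plan gives no figure for reporting bias, so the shift below is an assumption. Inputs: 424 students per arm (Section 3.11), independent t-test at the 0.05 level (Sections 3.17 and 3.17.3), normal approximation, no true effect, clustering ignored.

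- Standard error of the difference = √(2/424) = 0.0687 SD.
- Shift of 0.1 SD: z = 0.1/0.0687 = 1.46. Rejection = Φ(1.46 − 1.96) + Φ(−1.46 − 1.96) = 0.307.
- Shift of 0.2 SD: z = 0.2/0.0687 = 2.91. Rejection = Φ(2.91 − 1.96) + Φ(−2.91 − 1.96) = 0.829.
- No shift: 0.05.

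**3. Scale, smoking.** Take the planning rate of 0.088 (Section 3.6) as the true rate in both arms, and assume that a fraction c of the intervention-school students who smoke deny it. The reported rate in that arm is 0.088 × (1 − c). With 424 per arm, a two-sided two-proportion test and clustering ignored:

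| c (assumed) | Reported rate, intervention arm | Declared significant |
|---|---|---|
| 0 | 0.0880 | 5% |
| 0.1 | 0.0792 | 7.5% |
| 0.2 | 0.0704 | 16% |
| 0.3 | 0.0616 | 31% |
| 0.5 | 0.0440 | 73% |

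To imitate the whole planned difference, 0.088 against 0.032, c would have to be 1 − 0.032/0.088 = 0.64.

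These figures show how sensitive the comparisons are to any differential reporting. They do not show what the script itself contributes. Modelling the clusters would change the rejection rates but would not take the bias out of the estimate.

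**The case against.** The strongest reply is that the script is one route of disclosure among several, and that the form already contains safeguards. Section 3.11 has the objectives explained to all students at enrolment, and six months of visits make the aim plain. The script itself asks for truthful answers and promises confidentiality. Section 3.12.2 keeps smoking and alcohol status from school authorities, teachers and parents, and Section 3.18 uses code numbers. The smoking, alcohol and activity sections tell students that no answer is right or wrong, and those statements sit closer to the items than the opening script does. Some items also point to the programme by themselves: item 80 asks about encouragement by the school, items 94 to 96 about the student's risk-reduction skills, and item 98 about behaviour-change skills.

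All of this stands as mitigation and as a limit on what rewording can achieve. None of it is a reason to repeat the hypothesis aloud at the moment of measurement, and three exposed sections lack the neutral statement.

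Three stronger readings might be inferred, and the protocol does not support them. The first is that all seven primary outcomes are open to favourable reporting; knowledge is a scored test. The second is that the cue always favours the intervention; that direction is plausible but not shown, since taught students might also judge their habits more strictly. The third is that the 31% and 83% are the consequence of this wording; they describe an assumed total shift from every source.

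**Conclusion.** The point holds for six of the seven primary outcomes. The protocol fixes a title and a read-out script that state the hypothesis and its direction to unblinded students just before they report their own behaviour and attitudes, and the same form serves at six months. This is an avoidable cue that can encourage favourable reporting in the intervention schools.

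Its size cannot be derived from the documents. The illustration (about 31% or 83% declared significant for a total shift of 0.1 or 0.2 SD) rests on an assumed shift, no true effect, 424 per arm and independent observations. It shows only that modest differential reporting would matter here. The protocol contains no contradiction or numerical error on this point. The case for acting is that the cue is unnecessary and cheap to remove, and that the protocol already uses neutral wording elsewhere in the form.

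**What to change.** Replace the title and the read-out script on the student form with neutral wording, identical in all four schools and at both time points. For example, call it a student health and lifestyle questionnaire, and say that the study wants to learn about the health habits of secondary school students. Remove any mention of an intervention, a module or effectiveness from the title and script. Keep the sentences on truthfulness and confidentiality. State that no answer is right or wrong for the behaviour and attitude sections, including diet, motivation and behavioral skills; the knowledge section, which is scored against a key, should be excepted.

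The consent information stays as it is. The cost is a few lines of the form and a minor ethics notification. The change reduces the bias but does not eliminate it, because the objectives are explained at enrolment and some items still refer to the programme's skills. The report should therefore still name differential self-report as a limitation of the six outcomes.

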**Please read the questions clearly and circle the appropriate response**

**1*.* Date of birth (DD MM YYY)**

**DOB**

**2. Age (in years)**

**AGE**

**3. Gender** 1. Male 2. Female **GENDER**

**4. In what grade are you?** 1. SHS

1

2. SHS

2

3. SHS

3

**GRADE**

**5. Ethnicity ETHNIC**

Other

| 11. Akan | 12. Banda | 13. Basare | 14. Bawule | | 15. Bimoba |
| --- | --- | --- | --- | --- | --- |
| 16. Chokosi | 17. Degarte | 18. Dagomba | 19. Ewe | | 20. Frafra |
| 21. Fulani | 22. Ga-Adangbe | 23. Gonja | 24. Grusi/ | | 25.  Konkomba |
|  |  |  | Kasina/Namkana | |  |
| 26. Kusasi | 27. Mamprusi | 28. Mo | 29. Pantra | | 30. Sefwi/  Wassa/Aowin |
|  |  |  |  |  |  |
| 31. Sisala | 32. Wala | 33. Wangara/ | 34. |  | |
|  |  | Dwula/ | (specify) |  |  |
|  |  | Zambraba |  |  |  |

**6. Which region are you from? REGION**

| 1. Ashanti | 2. Brong Ahafo | 3. Central | 4. Eastern |
| --- | --- | --- | --- |
| 5.Greater  Accra | 6. Northern | 7. Upper East | 8. Upper West |
| 9. Volta | 10. Western | 11. Other (specify) |  |

**7. Monthly pocket money POCMONEY**

| 1. < 50 | 2. 50-99 | 3. 100-149 | 4. 150-  199 | 5. 200-249 | 6. >250 |
| --- | --- | --- | --- | --- | --- |

**8. Father’s Education FAEDU**

| 1. None | 2. Primary school | 3. JHS | 4. SSS |
| --- | --- | --- | --- |
| 5. Diploma | 6. HND | 7. Degree | 8. Master and higher |

**9. Father’s Employment FAEMPLOY**

| 1. | Not 2. Clerical/Secretarial | | 3. Trader | 4. Farmer | |
| --- | --- | --- | --- | --- | --- |
| employed |  |  |  |  |  |
| 5. | | 6. Professional (teacher, banker,  health worker, administrative, etc) | 7.Labourer/ | 8. | Other |
| Tailor/Barber | |  | Domestic | (Specify) |  |
|  | |  | worker |  |  |

**10. Mother’s Education MOEDU**

| 1. None | 2. Primary school | 3. JHS | 4. SSS |
| --- | --- | --- | --- |
| 5. Diploma | 6. HND | 7. Degree | 8. Master and higher |

**11. Mother’s Employment MOEMPLOY**

| 1. | Not 2. Clerical/Secretarial | | 3. Trader/ | 4. Farmer | |
| --- | --- | --- | --- | --- | --- |
| employed |  |  | Food seller |  |  |
| 5. Seamstress/ | | 6. Professional (teacher, banker,  health worker, administrative, etc) | 7.Labourer/ | 8. | Other |
| Hairdresser | |  | Domestic | (Specify) |  |
|  | |  | worker |  |  |

**12. Who do you live with? LIVEWITH**

| 1. Both parents | 2. Father | 3. Mother |
| --- | --- | --- |
| 4. Aunt/Uncle | 5. Grandmother/father | 6. Other (Specify) |

**13. How many people are living with in your home household, including you**

**LIVEHOME**

| 1. One (If you are the only | 2. Two | 3. | 4. Four | 5. Five | 6. | 7. |
| --- | --- | --- | --- | --- | --- | --- |
| one) |  | Three |  |  | Six | Seven |

**14. Is there family history of obesity?**

1. Yes 2. No **FHBESITY**

**15. Is there family history of hypertension?** 1. Yes 2. No **HISBP**

**16. Is Cardiovascular Disease a major public health problem of today? PHCVD**

1. Yes 2. No 3. I don’t know

**17. How do you describe your health? HEALTH**

| 1. Excellent | 2.Very good | 3. Good | 4. Fair | 5. Poor |
| --- | --- | --- | --- | --- |

**SECTION 2 : DIET ASSESSMENT**

This refers to your diet over the past 7 days (one week). Please write the number of each food item consumed and circle the corresponding frequency of consumption

| **18. Fruits &**  **Vegetables** | **Handy measure** | **Number**  **consumed** | **(1) Never** | **(2) 2-3**  **Times per week** | **(3) 4-5**  **Times per week** | **(4) 6 Times**  **per week** | **(5) Daily** |
| --- | --- | --- | --- | --- | --- | --- | --- |
| Banana | 3 Middle finger Size |  | 1 | 2 | 3 | 4 | 5 |
| Mango | Orange average size |  | 1 | 2 | 3 | 4 | 5 |
| Pawpaw | Empty sardine tin size |  | 1 | 2 | 3 | 4 | 5 |
| Pineapple | Empty sardine tin size |  | 1 | 2 | 3 | 4 | 5 |
| Orange | Orange average size |  | 1 | 2 | 3 | 4 | 5 |
| Pear | Large orange size |  | 1 | 2 | 3 | 4 | 5 |
| Tangerine | Empty milk tin size |  | 1 | 2 | 3 | 4 | 5 |
| Watermelon | Empty sardine tin size |  | 1 | 2 | 3 | 4 | 5 |
| Cabbage | Stewing spoon level |  | 1 | 2 | 3 | 4 | 5 |
| Carrots | Stewing spoon level |  | 1 | 2 | 3 | 4 | 5 |
| Cassava  leaves | Stewing spoon level |  | 1 | 2 | 3 | 4 | 5 |
| Kontomire  (green leafy vegetable) | Stewing spoon level |  | 1 | 2 | 3 | 4 | 5 |
| Cucumber | Empty small tomato tin  size |  | 1 | 2 | 3 | 4 | 5 |
| Okro/okra | Stewing spoon level |  | 1 | 2 | 3 | 4 | 5 |
| Onions | Table spoon/big spoon  level |  | 1 | 2 | 3 | 4 | 5 |

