**3.12.2 Questionnaire**

The questionnaire will be pre-tested and assisted self-administered questionnaire in English language as in Appendix. The questionnaire will be divided into ten sections namely, socio demography, dietary intake, smoking, alcohol consumption, physical activity, CVD knowledge, motivation, behavioral skills, BMI (weight and height), and blood pressure (diastolic and systolic). The questionnaires will be administered in a classroom setting in all the selected schools.

Section one of the questionnaire will be used to access students’ age, gender, grade, ethnicity, monthly pocket money, and family history. Data on age will be collected in the form of open ended question and students will fill in the blank space provided. The rest (ethnicity, gender, religion, and family history) are in the form of closed ended questions and students are to choose the answers that will pertained to them.

Section two is a seven-day dietary recall instrument which are foods items mostly consumed in Ghana, the Ghana Demographic and Health Survey, (GDHS), (GSS, 2009; Nti, 2008) to assess dietary consumption. Amounts of each food intake will be stated with the use of handy measure tables (food weights). This are based on the weights of foods with their equivalent handy measure tables which are commonly used

in Ghana (Owusu, Ankrah, Boateng, & Anteh, 1995). Then frequency of consumption of certain foods will be scored based on one (1) for never dietary consumption, two (2) for 2-3 times per week, three (3) for 4-5 times per week, four (4) for 6 times per week, and five (5) for daily intake of a particular food item.

Section three and four are the modified smoking and alcohol questionnaires, Global Youth Tobacco Survey (GYTS) developed by WHO and Centre for Disease Control and Prevention (CDC) (CDC, 2008). It is a school-based adolescents’ self- administered questionnaire which comprised of a set of core questions that will be used to evaluate tobacco and alcohol control and prevention programmes among secondary school students. Students would be classified as never, ever, and current smokers and alcohol consumption. Strict confidentiality will be ensured among researchers to avoid disclosure of smoking and alcohol statuses to school authorities, teachers, or parents.

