**3.16.6 Diet Practices**

This referred to the total frequency in scores and amount of diet for each food item. Consumption of foods such as fruits, vegetables, seafood, and water were considered as healthy foods while the consumption of foods such as fried foods, fried eggs, fried chicken, fats and oils, plain sugar, sweet snacks, salted fish, and carbonated drinks are considered as unhealthy foods.

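### The diet form does not say whether 'Number consumed' is the 7-day total or the quantity per occasion, so the amount part of the dietary-intake primary outcome is ambiguous by a factor of about 2 to 7

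*Protocol*

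**What the plan says.** Section 3.15.2 lists dietary intake among the primary outcomes: "The primary outcomes are CVD knowledge and its risk factors, motivation, behavioral skills, physical activity, smoking, alcohol consumption, and dietary intake". Section 3.16.6 defines diet practices: "This referred to the total frequency in scores and amount of diet for each food item". So there are two components, a frequency score and an amount.

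Section 3.12.2 fixes the frequency score, running from 1 for never up to 5: "and five (5) for daily intake of a particular food item". On the amount it says: "Amounts of each food intake will be stated with the use of handy measure tables (food weights". It gives no formula that takes the student's entries to an amount.

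The data come from Appendix A, Section 2. It opens with the recall period, "This refers to your diet over the past 7 days (one week", and continues: "Please write the number of each food item consumed and circle the corresponding frequency of consumption". In items 18-25 each row has a portion-sized handy measure, a column headed only 'Number consumed', and the frequency categories (never; 2-3, 4-5 or 6 times per week; daily). Item 26, water, keeps the same number column, but its row is labelled as daily, its categories are mostly per day and its measure is a 500 ml sachet.

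**The concern.** The number sits between a single-portion measure and a times-per-week scale, and it is asked for together with a corresponding frequency. A student who eats one orange every day can reasonably write 1 (one each time, daily) or 7 (seven in the week). If the number is per occasion, the weekly amount needs multiplication by frequency. If it is already the weekly total, multiplying counts frequency twice.

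The amount bears on hypotheses 6 and 7 in section 1.6, and dietary intake is to be tested by t-tests and repeated measures ANOVA under section 3.17.3. If students split between the readings, the amount variable mixes two scales. A statistical analysis plan, which is not at hand, could supply the scoring rule. It could not repair a mixture of answers once they are on paper. The point therefore concerns the wording of the form, which this document fixes.

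**Working it through.** The documents state no figure for food amount, so there is nothing to reproduce. The check is direct arithmetic.

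**Inputs.** Frequency categories from Appendix A, items 18-25. Assumption: one handy measure per occasion and, for daily foods, one occasion per day. Let f be the number of occasions in 7 days.

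**Step 1: what the same diet produces.** A per-occasion reader writes 1 and a weekly-total reader writes f. Scored as a 7-day total, the entries give 1 and f. Scored as number × frequency, they give f and f × f. The ratio is f either way.

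| Category | f | Scored as 7-day total | Scored as number × frequency | Ratio |
|---|---|---|---|---|
| 2-3 times | 2 to 3 | 1 vs 2 to 3 | 2 to 3 vs 4 to 9 | 2 to 3 |
| 4-5 times | 4 to 5 | 1 vs 4 to 5 | 4 to 5 vs 16 to 25 | 4 to 5 |
| 6 times | 6 | 1 vs 6 | 6 vs 36 | 6 |
| Daily | 7 | 1 vs 7 | 7 vs 49 | 7 |

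For never, both amounts are zero. The range is 2 to 7, and 7 applies only to daily foods.

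**Step 2: noise from a mixture.** Suppose a share q of students eating one portion daily write 1 and the rest write 7. The shares are assumed. Mean = q × 1 + (1 − q) × 7; SD = 6 × √(q(1 − q)).

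- q = 0.10: mean 6.4, SD 1.8
- q = 0.25: mean 5.5, SD 2.6
- q = 0.50: mean 4.0, SD 3.0

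All of this spread is artefact, because the diets are identical.

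**Step 3: attenuation.** Suppose a food moves from 3 to 5 occasions a week at one portion each, and the number is scored as the 7-day total. Weekly readers record +2 and per-occasion readers record 1 both times, so 0. The mean recorded change is 2 × (1 − q): 1.8, 1.5 or 1.0 for the same three shares. Under number × frequency the distortion runs the other way: weekly readers go from 9 to 25.

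**Step 4: can the reading be recognised afterwards?** In part. An entry of 1 with daily circled does not fit a weekly total of whole portions, which would be at least 7. An entry of 7 with daily fits one each day or seven each day, and the latter is possible for items measured as a single toffee or biscuit. An entry of 3 with 2-3 times fits three in the week or three each time. Multi-portion and fractional-portion foods remain undecidable.

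**The case against.** The strongest reply is that the form does set a period. The sentence just before the instruction refers to the past 7 days, and section 3.12.2 describes a seven-day recall instrument, so a weekly total is a plain reading. Water is marked as the daily exception, which supports a weekly default elsewhere. This stands as far as it goes: the two readings are not evenly balanced. It does not settle the matter. Item 50 on alcohol uses nearly the same instruction with categories that include once a month and no 7-day window, and there only a per-occasion count fits well. Item 34 on smoking shows that the form can fix a unit when it wants to, since it asks for the usual number of cigarettes on smoking days.

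A second reply is that safeguards exist: "The questionnaire will be pre-tested and assisted self-administered questionnaire in English language". Section 3.13.2 also has 50 students rate clarity. That lowers the risk. But no counting instruction is given to students or helpers, and a student confident of either reading could rate the item clear.

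A reader might infer that the amount cannot be derived at all. The documents do not support that: it can be derived once a reading is assumed, and some mismatched answers show themselves. A reader might also infer bias between arms, because only intervention students are taught about intake and food selection between the visits. The topics in Table 3.4 concern health effects, food selection and behaviour, not how to fill in the box, and section 3.11 gives both arms the same questionnaire at both times. A differential shift is possible but not shown.

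**Conclusion.** The point holds as an ambiguity in one column of a data-collection form. The amount component of dietary intake is uncertain by a factor of 2 to 7 depending on how often a food is eaten, assuming one portion per occasion; 7 is the maximum, not the typical value. The consequence to expect is added variance and, if the number is scored as a weekly total, attenuation of real change. How large this is depends on the share of students taking each reading, which the documents do not give; the shares of 10% to 50% used above are assumptions.

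The problem is confined to the amount. The 1-5 frequency score does not use the number and is unaffected, and so are the other primary outcomes. A spurious group-by-time effect would need the reading to shift by different amounts in the two arms, for which there is no evidence.

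**What to change.** Before baseline:

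- Head the number column for items 18-25 'total number of handy measures eaten in the past 7 days', and for item 26 'number of sachets per day'.
- State in section 3.16.6 that weekly amount = number × handy-measure weight for foods, and number × 7 × 500 ml for water.
- Check at the planned pre-test that students fill in the box as intended.
- Use the identical form at baseline and at six months, so that the heading itself introduces no shift between visits.
- Keep the frequency score as the outcome component already defined in sections 3.12.2 and 3.16.6, and use it in addition as a consistency check on the amount.

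Per-occasion wording would also remove the ambiguity. The 7-day total is preferable because multiplying a per-occasion count by a banded frequency leaves a factor of up to 3/2 = 1.5 in the 2-3 band and 5/4 = 1.25 in the 4-5 band.

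The cost is one heading per table and one sentence in 3.16.6. The small downside is slightly more recall effort for students.
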